### Intervention overview

Our community-academic team designed TRUE HAVEN, a community-based intervention that acts on two leverage points in our community’s systems that are most feasibly intervened upon and projected to be most impactful: (1) housing stability (for recently incarcerated individuals as well as family members of incarcerated people) and (2) mental well-being. We will study the effect of our intervention using a cluster-randomized, stepped-wedge study design. Each of six neighborhood’s residents will be eligible for enrollment in the housing stability component of the initiative for a 6-month period and during this time, trusted community members in this neighborhood will be trained in trauma-informed counseling. In addition, TRUE HAVEN will employ the Learn As You Go (LAGO) approach [27] that analyzes intervention implementation and outcome data at each trial stage to tweak and tailor the intervention as the trial progresses to optimize the cost-effectiveness of the package, mitigating the risk of an intervention failure. LAGO will provide rich contextual and experiential data for our evaluation of the intervention package.

#### Housing stability

TRUE HAVEN aims to mitigate the effects of structural racism by fostering housing stability and supporting home ownership among people affected by incarceration, including those that have a family member incarcerated and individuals returning to the community from prison. We will partner with local organizations to provide increased access to low-interest home loans and down payment or rental assistance to participants needing financial support. All participants receiving these financial supports will engage in a comprehensive, milestone-based financial education program through the ULSC or Neighborhood Housing Services (NHS) to learn how credit scores impact purchase power, financial terms in banking, managing unexpected expenses, preparation for an emergency expense, and developing habits to budget monthly spending. All participating organizations have agreed there will be accessing financial supports or leases or loans without considering family member’s or personal history of incarceration. We plan to support 1,400 individuals returning to the community from incarceration and/or their family members (i.e., spouse/partner, co-parent of a child, parent, sibling, or child) from these 6 neighborhoods. In addition, as part of its usual services, ULSC or NHS will also connect participants to job training and employment opportunities, as needed.

#### Mental wellness

We will partner with Clifford Beers Community Health Partners, an integrated network of care that offers “wrap around” mental health and social services to children and families, to train community members (e.g., barbers, faith leaders, youth mentors, educators) on the impact of trauma so they can recognize those affected by the trauma of gun violence and be able to properly support them, engage them in skill building to effectively regulate emotions, and connect them to formal mental health resources, if needed [3]. The purpose of the training is to offer education on trauma prevalence and research on childhood adversity as well as its potential long-term impacts; how to recognize the impact of trauma on the body, brain and behaviors and an opportunity for dialogue about various types of trauma impacting the community (acute, chronic, historical, race-based and systemic trauma) and to share common language regarding how trauma and stress affect the community’s overall wellbeing. Trainings will also include discussion on how to actively support and refer people in need of formal mental health treatment through support from partnered community health workers. We anticipate training at least 50 trusted community members from the target neighborhood in trauma-informed care and counseling each half-year. We will work with our community partners and local neighborhood groups to recruit participants for these trainings. We aim to recruit a diverse group of community members, including youth mentors, barbers, faith leaders, teachers, and other local influencers, who will then interact with community members as they encounter them in the course of their work and lives.

#### Coalition to address structural racism

We will convene a coalition of diverse stakeholders quarterly to elicit and review barriers to achieving housing stability and accessing mental health supports for our participants and to actively and collectively work to address these barriers. This Steering Committee (SC) is inclusive of CAB Members and augments this group with additional leaders at the local, city, and state levels, such as city and state officials, local and regional philanthropy, local businesses, law enforcement, and physical and mental healthcare and other social service providers and leadership of coalitions representing these providers. The TRUE HAVEN SC is well-suited to both identify policy and programmatic barriers to achieving equitable access to stable housing and mental healthcare as well as to collaboratively find and enact solutions to address such barriers. The SC will meet quarterly, review data on ongoing study outcomes, review information on barriers that have arisen to housing stability and accessing mental healthcare, and will engage in facilitated processes to propose and enact plans to address those barriers. We will track the number of barriers identified and initiatives enacted to address them at the local, city, and state levels over time.

#### Inclusion and exclusion criteria

The primary outcome of TRUE HAVEN is a community-level outcome, incidence of neighborhood gun violence, and, as such, there are no inclusion or exclusion criteria. However, for the housing assistance intervention component, individuals are eligible for study entry if they: (1) live in one of the six neighborhoods with highest rates of gun violence in New Haven, CT, including Hill North & South, Fair Haven, Newhallville, Dixwell, West River/Dwight and Beaver Hills/Edgewood (Fig. 1); (2) are over 18 years of age; (3) were previously incarcerated within the last 12 months or have a family member who is currently incarcerated (i.e., spouse/partner, co-parent of shared child, sibling, parent, child). The rationale for these criteria is to target people who are at high risk of eviction and social instability when their family unit has been disrupted by incarceration, which is associated with involvement in gun violence. Individuals are excluded if they plan to leave the study area within 1 year. This exclusion criterion excludes participants who are unable to complete follow up and thus unable influence or be influenced by neighborhood changes. Concomitant interventions are permitted.

#### Recruitment, procedures, and follow-up

For the housing stability component, the recruitment and assessment processes are described above and summarized in Fig. 2. The hypothesized determinants were originally developed based on the Consolidated Framework for Implementation Research (CFIR) and grouped by levels [28]. Participants meeting the inclusion criteria and who consent to participate will complete a baseline assessment on the day of enrollment. Participants will then engage in a comprehensive, tailored financial education and counseling program through the ULSC to address their housing instability. The education component includes learning objectives such as understanding how credit scores work, creating and maintaining a budget, developing habits to save money, setting sound financial goals, and avoiding debt. The financial education program is milestone-based, so participants move forward to the next lesson only after prior content has been mastered. This approach fosters self-efficacy and confidence and ensures graduates of the program are equipped with the skills needed to maintain financial security after financial supports expire. Financial supports in the form of rental assistance or down payment assistance and/or low-interest home loans will be provided to participants when the appropriate milestones have been achieved. Most people are able to complete the financial education program within six months. At the beginning and end of their course, participants will complete a knowledge assessment to assess their understanding of financial topics (e.g., how credit reports work and how much money should be in savings) and their perceptions of the acceptability, appropriateness, and feasibility of the program. At the time of enrollment and at 6-months, 1-year and 2-years, ULSC will contact participants by phone to assess their housing situation (i.e., they remained in their home/apartment, moved to a different home/apartment and if so why, were evicted, underwent foreclosure) and financial situation (i.e., how much in savings). We will also assess other outcomes such as self-efficacy, perceived health and well-being, and financial knowledge.

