**Fig. 2 Fig2:**
[figure not shown]
Logic model describing the multi-level, multi-component TRUE HAVEN intervention and measurable outcomes

In addition, a subset of participants in each neighborhood will be asked if they are willing to participate in a focus group to explore implementation outcomes (e.g., satisfaction with the intervention and content delivery, perceived usefulness of the intervention) in the second half of or right after their 6-month enrollment period. These focus groups will include a purposive sample of 20 participants each half year, stratified by gender, race, and age, and each focus group will have no more than 8 participants. We will hold separate focus groups with men and women to understand if and how various factors affect men and women differently. The focus group will be no longer than 90 min in length and participation will be voluntary – the participants will still be able to complete the other parts of the program if they elect not to join the focus group. We will also collect data on implementation outcomes (i.e., adoption, acceptability, feasibility, appropriateness) from the staff members delivering the financial education (i.e., housing counselors; other ULSC staff). This will be in the form of bi-annual assessments programmed in Qualtrics and administered by the program manager of this study in person or over the phone. We will also recruit a sample of staff for focus groups yearly to qualitatively explore these outcomes. Participant dropout and retention will be monitored.

The above procedures all refer to the housing assistance part of the intervention. In addition, we will also recruit 50 community members from each neighborhood to be trained in trauma-informed counseling by our partners at Clifford Beers Clinic. We will ask them to track and report the number of people they counsel each week to the program manager. Some of them may be asked to participate in implementer focus groups as well. Outcomes will be assessed in aggregate at the neighborhood level, including how many people were newly referred for mental health care and neighborhood rates of depression, anxiety, and symptoms of post-traumatic stress. Still, we will not be obtaining data directly from the individuals who are counseled or seek mental health care.

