#### Implementation outcomes

Following the RE-AIM implementation science framework [25], assessments on implementation outcomes are collected by research coordinators at baseline and every six months following the initiation of the intervention in each neighborhood. We will use validated scales to assess implementation outcomes, including measures of acceptability, appropriateness, and feasibility by Weiner, et al [18], and measures of fidelity and reporting adaptations and modifications following the Framework for Reporting Adaptations and Modifications-Enhanced (FRAME) [34].

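### The participants' closing ratings and knowledge test are tied to the end of a mastery-gated course, so read literally they are completers' results; they should be collected from everyone enrolled at the existing 6-month contact

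*Protocol article*

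**What the plan says.** All of this concerns the housing stability component.

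- **Closing assessment** (Recruitment, procedures, and follow-up): "At the beginning and end of their course, participants will complete a knowledge assessment". The same sentence adds "and their perceptions of the acceptability, appropriateness, and feasibility of the program".
- **Progression** (same section): "participants move forward to the next lesson only after prior content has been mastered". On duration it says only "Most people are able to complete the financial education program within six months". No completion rate is stated.
- **Calendar contacts** (same section): "At the time of enrollment and at 6-months, 1-year and 2-years, ULSC will contact participants by phone", to ask about housing and finances. Financial knowledge is then named among further outcomes, without its own schedule. Data collection also places questionnaires at 6 months, 1 year and 2 years.
- **Implementation outcomes**: scales for the same three constructs are collected "at baseline and every six months following the initiation of the intervention in each neighborhood". The respondents are not named.
- **Focus groups** (Recruitment, procedures, and follow-up, after Fig. 2): "a purposive sample of 20 participants each half year, stratified by gender, race, and age", held in the second half of the person's 6-month enrollment period or just after it.
- **Adaptation** (Intervention overview): the Learn As You Go approach "analyzes intervention implementation and outcome data at each trial stage to tweak and tailor the intervention as the trial progresses".
- **Table 2** lists acceptability and appropriateness at individual/family level under Effectiveness, and acceptability, appropriateness and feasibility at implementer level under Adoption.

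**The concern.** A course in which each lesson must be mastered before the next has an end only for those who get through it. A participant who stalls or leaves has no defined closing time point and, on the stated rule, gives no closing rating and no closing test.

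Two results are affected. The end-of-course ratings would describe people the program suited well enough to finish, so the figure could look best when the program loses those it suits least. The pre/post knowledge change would be measured in people for whom mastery was a condition of reaching the second test, so part of the gain is built in, to the extent that the test covers the lesson content.

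The reasons people stop would also be missing from the quantitative ratings, although they matter to anyone improving the course.

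**Working it through.** **1. Figures in the plan.** No sample size or power figure depends on this point. The enrollment used below is the plan's 1,400, which agrees with its own breakdown: 1,400 / 6 = 233.3 per neighborhood (stated 233), and 1,400 / (6 × 7) = 33.3 per neighborhood per step (stated 33).

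**2. Does another provision collect the closing items from people who stop?**

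| Provision | Depends on finishing? | Supplies the closing items for stoppers? |
|---|---|---|
| Start-of-course rating | No | No: it precedes experience of the course |
| 6-month, 1-year and 2-year contacts | No | Possibly for financial knowledge, named just after them; the three rating scales are not assigned to them |
| Six-monthly implementation scales | No | Unclear: respondents not named, and the clock is the neighborhood's, not the participant's |
| Focus groups; client interviews (Table 1, process evaluation) | No | Possibly, as qualitative data; course status is not a stratum |
| Dropout monitoring; completion percentage | No | No: these count stoppers but do not record their views |

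The third row can be read two ways. If the six-monthly scales cover participants, the same constructs have two clocks, and the article does not say which one feeds Table 2. If they cover staff, which would match the twice-yearly staff assessments, the start-and-end-of-course rule is the only stated timing for participants' quantitative ratings. Both readings need clarification.

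**3. Does weighting repair it?** Statistical analyses plans inverse probability weighting for missing outcomes. If ratings are taken only at course end, a person who stops has zero probability of giving one. Weighting on other covariates must then assume that stoppers would have rated the program as finishers with the same measured covariates did. That assumption is the point in doubt.

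**4. Illustrative size.** Let c be the share completing, A the mean rating (or share favorable) among completers, and B the same among non-completers.

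- Completers-only figure: A
- All-enrolled figure: cA + (1 − c)B
- Overstatement: A − [cA + (1 − c)B] = (1 − c)(A − B)

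The document gives neither c nor A − B, so both are assumed. Overstatement in percentage points:

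| c | Without a closing rating, 1,400(1 − c) | A − B = 10 | A − B = 20 | A − B = 30 |
|---|---|---|---|---|
| 0.9 | 140 | 1 | 2 | 3 |
| 0.8 | 280 | 2 | 4 | 6 |
| 0.7 | 420 | 3 | 6 | 9 |
| 0.6 | 560 | 4 | 8 | 12 |
| 0.5 | 700 | 5 | 10 | 15 |

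The result follows the assumptions closely. With A = 80% and B = 40%, completion of 80%, 65% and 50% gives all-enrolled figures of 72%, 66% and 60%, an overstatement of 8, 14 and 20 points.

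**The case against.** The strongest reply is that this is a wording gap in a condensed article. The end of the course could mean the end of a person's participation, and the article uses a different word, graduates, for those who complete. The participant flow diagram and the SPIRIT diagram are not visible in the text at hand, and the full protocol may say when early stoppers are assessed. Much collection does not depend on finishing, and neither the ratings nor financial knowledge is a primary or listed secondary outcome. Financial knowledge does not appear in Table 2 at all.

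Much of this stands, and it rules out several stronger readings that a reader might infer:

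- **That the acceptability and knowledge results as a whole exclude people who stopped.** Financial knowledge is named again after the calendar contacts, and interviews and focus groups are not limited to finishers.
- **That the adaptations rest on completers' ratings.** Intervention overview describes implementation and outcome data generally. These ratings are one input among others, and no text makes them the driver.
- **That closing ratings at each stage come from the fastest finishers.** This requires a trial stage to end with each 6-month window, and the article does not define a stage.
- **That the two schedules contradict each other.** Without named respondents, a contradiction is possible but not shown.
- **That the bias has a known size.** Every figure in step 4 of the working rests on assumed inputs. The 50% rows also sit uneasily with the statement that most people can finish within six months.

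What the reply does not remove is the rule itself. The article does not merely leave the timing open: it names the end of a mastery-gated course as the time point, and nothing else in it clearly assigns the closing ratings to people who do not get there.

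**Conclusion.** The point holds in a limited form. Taken as written, the end-of-course ratings of acceptability, appropriateness and feasibility, and the pre/post knowledge change, are completers' results. They may be too favorable by an amount the document does not allow to be calculated; the 1 to 15 points of the main table show only how the bias scales under assumed completion and rating gaps. The conclusion rests on reading the end of the course as completion of its gated lessons, which is the natural reading but not an explicit definition. The six-monthly schedule under Implementation outcomes does not clearly resolve it. The primary outcome, the listed secondary outcomes and the sample size are unaffected. The correction is worth making because one affected measure is a Table 2 Effectiveness outcome and the remedy uses a contact that already exists.

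**What to change.** 1. Collect the three ratings and the closing knowledge test at the scheduled 6-month participant contact, from everyone enrolled and whatever their course progress.
2. At that contact, record course status (finished, still in the course, stopped) and, for those who stopped, the reason.
3. Report the ratings and the knowledge change for all enrolled as well as for completers, labeled as such.
4. Reconcile Recruitment, procedures, and follow-up with Implementation outcomes and Data collection by stating who responds to which scale, and whether the clock is the participant's or the neighborhood's.

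Adding course status as a focus-group stratum is optional: the sample is only 20 per half year and is already split three ways. Restricting adaptation decisions to participants who have reached six months is not recommended as a requirement, because it would make those data a step older.

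The cost is revised wording and a slightly longer 6-month contact, with no added visit. The change will not remove selection altogether, since people who stopped are also likelier to miss the contact. However, they then have a chance of being observed, and non-response can be reported by course status.

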***Maintenance***				
Maintenance of fidelity and delivery	Implementers	Quantitative/Mixed	All	PM/Implementers
New structures, policies, practices and values that address structural racism	Neighborhood/ City	Quantitative/Mixed	All	Implementers/ Investigators
# and % participants that remain in their home for > 2y	Individual/family	Quantitative	H	Implementers
% families/individuals evicted or homes foreclosed	Neighborhood	Quantitative	H/F	CHFA
$ amount of home loans administered each year	Neighborhood	Quantitative	H	CHFA
# and % participants that kept job for > 2 years	Individual/family	Quantitative	F	Implementers
Social cohesion trend	Neighborhood	Quantitative	T	DataHaven
Yearly incidence of gun violence trend	Neighborhood	Quantitative	All	NHPD
Collective well-being trend	Neighborhood	Quantitative	All	DataHaven

Following the principles of community-based participatory research, all aspects of this project -- from study design, through resource governance, and implementation -- have been achieved through collaborating with community partner organizations. A Community Advisory Board (CAB) that is comprised of racially and ethnically diverse community members living in neighborhoods with high rates of gun violence, firearm assault survivors, formerly incarcerated people, leaders of community-based organizations, educators, academics, city officials, youth mentoring programs, violence deterrence programs, probation officers, and physical and mental healthcare and other social service providers, has been overseeing and guiding this work for more than a decade. Coordinated by the Urban League of Southern Connecticut (ULSC), a regional civil rights organization that aims to empower economically disadvantaged people and groups to secure and sustain economic self-reliance and parity among communities in Connecticut, the CAB meets monthly and will deliver or support delivery of relevant intervention components, as listed in Supplemental Table 1.

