#### Data collection

For the primary outcome, the New Haven Police Department will provide neighborhood-level data on gun assaults. DataHaven, a not-for-profit organization that collects neighborhood-level data on community wellbeing and social cohesion, is our key community partner who will provide neighborhood-level outcomes each year of our study. Connecticut Housing Finance Authority (CHFA) will provide neighborhood-level data on home ownership, loan denial, eviction and foreclosure. In addition, for participants recruited to the housing assistance program, information on sociodemographic backgrounds will be collected at the baseline, and questionnaires will be administered verbally either by phone or in-person at the 6-month visit by a housing counselor, and at the 1-year and 2-year time points by phone by the program manager. For qualitative and implementation outcomes, there may be additional *de novo* questions added that stakeholders think are important to include. Likewise, focus group questions will be developed in collaboration with our CAB and implementation partners and submitted to the IRB for approval prior to holding any focus groups.

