Further secondary analysis will involve the specific outcomes of the two key components of TRUE HAVEN -- housing and mental health services for families affected by incarceration. Each of these components acts at either the neighborhood, program/implementer or individual/family levels and will include different populations with different sample sizes. In general, the overall approaches to analysis described above will be taken. When outcomes are continuous, generalized estimating equations will typically use the identify link function, and when they are binary, they will use the log link function. If the outcomes are repeated within unit over time, a second random effect will be included to induce the correlation due to repeated measures within, say, individuals or implementers. Mediation analysis will be another informative feature of the statistical analysis plan. Here, we will assess the extent to which any improvements to neighborhood shooting rates are mediated by beneficial changes in downstream process outcomes due to the intervention. These process outcomes could include those given by the RE-AIM and Proctor frameworks in the project logic model presented in Fig. 2. Mediation analysis [38, 39] for downstream effects will use the difference method. Inverse probability weighting will be used to address missingness in outcomes, while missing indicator methods will be used to handle missing covariates when applicable.

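### Housing follow-up has no code for reincarceration or death, and weighting cannot recover these participants, so two-year home and job retention would tend to be overstated

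*Protocol article*

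**What the plan says.** All references are to the protocol article.

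- **Who is followed.** Under Inclusion and exclusion criteria, housing participants qualify if they "were previously incarcerated within the last 12 months or have a family member who is currently incarcerated". The split between the two routes is not given.
- **How they are followed.** Recruitment, procedures, and follow-up says that "ULSC will contact participants by phone to assess their housing situation" at enrollment, 6 months, 1 year and 2 years. Data collection differs slightly: "questionnaires will be administered verbally either by phone or in-person at the 6-month visit by a housing counselor". For the two later contacts it names only the telephone, with the program manager calling. Both sections leave phone as the only mode at 1 and 2 years.
- **What is recorded.** Housing status, introduced by i.e., is that the participant stayed, or "moved to a different home/apartment and if so why, were evicted, underwent foreclosure".
- **What depends on it.** The Maintenance block of Table 2 lists the number "and % participants that remain in their home for > 2y", and a matching item for keeping a job more than 2 years. Both are participant-level and assessed by implementers.
- **Absent outcomes.** Statistical analyses states: "Inverse probability weighting will be used to address missingness in outcomes". No exception is given.

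Participant reincarceration and death do not appear anywhere in the article as a status, outcome or event.

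**The concern.** Reincarceration is a foreseeable event in a cohort partly recruited on recent release, and death is foreseeable in neighborhoods chosen for their shooting rates. A participant in prison or dead at the 2-year call fits none of the four statuses and will rarely be reachable.

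Inverse probability weighting requires that every kind of participant has some chance of being observed. It lets respondents stand for similar non-respondents. Here the event itself removes the chance of responding and also settles the outcome: a person in prison at the contact is not living in the home or holding the job. Baseline covariates cannot repair this, because the event happens after enrollment and no respondent shares it. Death is different again. It truncates the outcome and is not ordinary missingness.

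What is at stake is the reported level of two-year home and job retention, which would look better the more often this kind of failure occurs.

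**Working it through.** The plan states no figure for retention, reincarceration or death, so there is none to reproduce. The check is therefore algebra with assumed inputs.

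**Inputs**
- p: share retained among the other, reachable participants. Assumed 0.70, with 0.60 and 0.90 as alternatives.
- q: share in prison or dead at 2 years. Assumed 5%, 15% or 25%.
- 1,400 participants (Justification of sample size), so q corresponds to 70, 210 or 350 people.

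**Step 1: affected participants counted as not retained.** Level = p(1 − q).

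**Step 2: affected participants treated as missing and weighted.** Let m be retention among the reachable participants who resemble them on the weighting covariates. The estimate is p(1 − q) + mq.

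**Step 3: overstatement.** Step 2 minus Step 1 = mq. If the covariates do not predict retention, m = p and the overstatement is pq. If they do predict it, and those at risk resemble people who do worse, m < p and the gap is smaller. It closes only if m = 0.

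| q | p(1 − q) at p = 0.70 | Overstatement pq at p = 0.70 | at p = 0.60 | at p = 0.90 |
|---|---|---|---|---|
| 5% | 66.5% | 3.5 points | 3.0 | 4.5 |
| 15% | 59.5% | 10.5 points | 9.0 | 13.5 |
| 25% | 52.5% | 17.5 points | 15.0 | 22.5 |

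**Step 4: dilution by family-member enrollees.** If only a share s entered through their own incarceration, a share r of those is affected, and family members are not affected, then q = s × r. With s = 0.50 and r = 0.15 (assumed), q = 0.075 and the overstatement at p = 0.70 is 0.70 × 0.075 = 5.25 points, half of 10.5.

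**Step 5: level versus contrast.** These are errors in one level. If two conditions 1 and 0 were compared, with m = p in each, the error in the difference would be p₁q₁ − p₀q₀. That depends on how p and q differ between conditions, on which the documents give nothing. It is zero if both are equal.

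The sizes above treat deaths as not retained. If deaths are kept apart as truncating events, q covers reincarceration only and p is read among survivors.

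**The case against.** The strongest reply is that the article nowhere says these participants are classed as missing. It is a condensed account, and response codes and rules for death or imprisonment may sit in case forms, the full protocol or the analysis plan. Its use of i.e. is also loose: the same sentence reduces the financial situation to savings, while Table 2 adds credit score and housing cost. The follow-up description omits job retention altogether, so it is not the full instrument. Some cases could be caught:

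- the question on why someone moved could record a return to prison;
- 6-month contact may be in person;
- someone jailed and released between contacts can answer the next call;
- the section on data storage mentions linked administrative databases;
- dropout is monitored.

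Much of this stands. Classification as missing is an inference, and the loss will not be total. It does not remove the point. No proxy respondent or alternate contact is described, the linkage is not tied to participant housing status, and contact at 1 and 2 years is by phone only. The article also fixes weighting for absent outcomes without exception. That choice does worse than recording a known non-retention.

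It is also fair that counting death as a housing failure is a choice of estimand, not a correction.

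**Conclusion.** The point holds for the level of the two participant-level Maintenance outcomes, home and job retention beyond two years. Followed as written, the plan would tend to overstate them by up to pq: 3.5 to 17.5 points at p = 0.70 and q from 5% to 25%. This rests on assumed rates, on affected participants being mostly unreachable, and on weighting covariates that add little. It is smaller if the covariates predict retention or if many enrollees are family members.

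A reader might infer more, which the documents do not support:

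- **That the bias exceeds what the trial can detect.** The 10 and 12 points under Justification of sample size are detectable intervention contrasts, at baselines of at most 20% and 40%. A gap in a level should not be set against them.
- **That the trial's main results are affected.** The primary outcome comes from police data. The secondary outcomes named in the article are not shown to be affected. The Connecticut Housing Finance Authority "will provide neighborhood-level data on home ownership, loan denial, eviction and foreclosure", which does not depend on reaching participants.
- **That the Learn As You Go adaptation is misled.** Two-year retention is not named as an input to it.
- **That savings are overstated.** A participant's savings are not known merely because the participant is in prison or has died, so the argument for home and job does not carry over.

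**What to change.** 1. Add reincarcerated and died, each with a date, to the status list at 6 months, 1 year and 2 years.
2. At enrollment, record an alternate contact, with consent, to be asked when the participant cannot be reached.
3. Count participants incarcerated at the contact as not remaining in the home and not in the job.
4. Report deaths separately, with a sensitivity analysis that counts them as not retained.
5. Restrict inverse probability weighting to participants whose status is truly unknown.

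The cost is a small addition to the form and the consent wording, a short analysis rule, and a reported retention that will look less favorable. Enrollment opened in February 2023, so this is best done early: status not recorded at the time is hard to reconstruct later.
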